### Statistical analyses

As mentioned above, our interest is in four potential endpoints, which we have prioritized according to clinical relevance. However, due to lack of experience with using these outcomes in this setting, we do not know whether they are measured in a reliable manner and whether they show a population variation which makes them suitable as an outcome in an RCT. For example, we cannot exclude that there is little variation in some of the intended outcomes across children or that we observe associations with baseline variables which are lower than expected and/or difficult to explain. Such insights may lead to a change in the prioritization of the outcome variables.

We will hence conduct an initial outcome data analysis. With respect to the three SMS questions we will inspect the individual trajectories regarding smoothness and visibility of improvements or deteriorations at the individual level. Next, we will relate the 4 weeks pre-intervention averages and standard deviations to all baseline characteristics and to each other in order to check whether the observed association patterns can be explained in a reasonable manner. With respect to the change from pre-intervention (four-week averages prior to intervention) to post-intervention (four-week averages at end of trial period) we will consider the joint distribution to judge the existence and magnitude of floor and ceiling effects and to inform the choice between absolute or relative changes. We will also depict the distribution of the change variables themselves, in particular with respect to the degree of variation. Further, we will compare the distribution of the three change variables to judge both the general association as well as specific combination patterns, for example the occurrence of a clear improvement in one question but a stagnation in another question. These analyses will also be stratified by age and gender to judge whether such characteristics may influence the degree and pattern of association. If no clear patterns emerge, the investigation will be extended to a multivariable analysis of all pre- and post-intervention measurements of the three questions. GPE will be included in the analysis of the change variables.

The initial outcome data analysis will be performed by an independent statistician, who will obtain a copy of the data set with baseline characteristics, the weekly results for the three SMS questions and the GPE of the first 100 children. No information on treatment group membership will be provided. The statistician will prepare a statistical report to be distributed among the research team. The research team and the statistician will discuss the results and prepare a further short report summarizing the insights gained and potentially deciding on a reprioritization. We do not use a priori defined criteria for the decision to change the prioritization. In general, many different properties may pop up which may influence the decision. Consequently, it is hard to pre-specify an algorithm. Initial outcome analyses have rarely been performed until now, so there is no established framework for this. However, the decision will be based on a combination of the statistical findings and theory. We will therefore report the entire process for clarity (statistical report as well as a transparent report of the decision process). All analyses will be blinded and we can therefore exclude any undue influence on the final results of the study. Both reports will be finished prior to randomizing the last child in the study and will be included in the supplementary material of the first research publication.

In the primary analyses, we will visualize and describe the distribution of the four primary outcomes in each treatment arm. Intervention effects will be assessed by considering the difference in mean values between the two treatment arms, reported together with 95% confidence intervals and *p*-values. In addition, Cohen’s effect size defined as the difference in mean values divided by the common standard deviation will be reported.

Multiplicity due to using four primary outcomes will be taken into account by applying the fixed sequence test principle [34] using the prioritization determined in the initial outcome analysis as the a-priori order of hypotheses. For all four primary outcomes, inference will be based on a least squares regression model. For each change score the baseline level will enter as covariate, and for the global perceived effect the number of days with headache per week will enter the model. In case the initial outcome analysis points to correlations between patient characteristics and outcomes above 0.3, these patient characteristics will be added as additional covariates. A responder analysis will be performed, reporting the proportion in each group reporting 20, 25, 50 and 75% improvement compared to baseline for the three change scores. Furthermore, numbers needed to treat, with success defined as 20% improvement, will be estimated.

Secondary outcomes will be analyzed similarly.

Patient and treatment characteristics as well as drop out frequencies and patterns will be described within each treatment group. Single missing values in the SMS data will be ignored, as long as there is at least one value available within the last 4-weeks periods. Patients with missing answers to all 4 weeks in last period will be ignored (complete case analysis). Missing values in baseline characteristic will be replaced by regression-based predictions from the other baseline variables, using least squares regression to predict continuous variables, and ordinary, ordinal or multivariate logistic regression for binary, ordinal and categorical variables.

Multiple imputation will be used to conduct sensitivity analyses with respect to handling missing values. These will be based on a chained equation approach (as implemented in Stata’s mi command) considering simultaneously all outcomes and baseline variables. Analyses of data will be conducted by a researcher, otherwise not involved in the project and who will be blind for the group coding. The clinical investigators will not be involved in the analyses.

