**Methods:**

Children with weekly headaches for at least six months will be included if they have indications for chiropractic manipulation. The participants will be randomized to either chiropractic manipulation or sham manipulation. Both children and parents will be blinded for allocation. There will be 100 children in each arm and they will answer weekly text messages four weeks prior to treatment and during a four months treatment period. Potential primary outcomes are weekly number of headaches, intensity of headache, medication use and global perceived effect. Secondary outcomes include side-effects and headache status after one year.

An initial outcome data analysis will be performed to inform the choice of primary outcome (adaptive design). Intervention effects will be reported as the difference in mean values between the two treatment arms, Cohen’s effect size and numbers needed to treat.

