#### Blinding

Blinding of the participating chiropractor in this trial is obviously impossible. Blinding of the participants is attempted by not revealing the group allocation and by including a sham manipulation that closely resembles the active treatment. Furthermore, eight visits are given in the sham manipulation group to resemble the estimated number of treatments in the chiropractic manipulation treatment group to reduce attention bias. Also, in the control group an activator treatment [33] used on the chiropractor’s own arm in order to produce a noticeable clicking noise resembling a joint cavitation. Blinding of the parents is attempted by not inviting them to observe the treatment. At the end of the treatment period, participating children and their parents receive a question asking them, which of the two groups they believe they have been participating in.

At all sessions in both groups, parents are allowed to be present during the interview where the chiropractor will ask about headaches, side effects experienced after the previous treatment according to a checklist (Additional file 8), and the participant will also be asked if he/she has experienced any trauma since the last visit, and if so, the characteristics of the trauma.

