#### Additional information collected during the trial period by the chiropractor

number of treatmentsarticulations treated (recorded at each visit)numbers, severity and character of traumas/accidents experienced between visits while participating in the trial (recorded at each visit)side effects experienced between two treatments (type, timing and duration; recorded at each visit)other diseases reported/identified during treatment periodnumber and reasons for drop-out

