The parent-child interaction may bias the answers of both child and parent [21] because there can be a discrepancy between the child and the parent’s report of the child’s headache [39]. Therefore, it is important that the same person reports on the text message headache diary every week during the entire trial and this represents a challenge for some children living in divorce families with inadequate communication between the parents. This is especially true for the SMS-question regarding use of medication because the children may not always be aware of what type of medication they receive and for what. Reporting of medication used can also depend on the age of the child. Some children are allowed to carry their own non-prescription medication for headache and use it according to own needs without asking the parents first, and therefore memory bias can be an issue in this age group.

A major strength of this study is its pragmatic nature, performed in a normal clinical setting, where the chiropractic manipulation treatment group receives treatment according to their individual needs in terms of areas in the spine being treated and the number of treatments given. In addition, parents and children in both groups can continue their usual self-care for headache if and when they want to. First of all, this allows us to investigate the specific effect of chiropractic manipulation and secondly, is a requirement for ethical reasons because we investigate children who suffer from recurrent and in some cases severe headache and/or migraine. Further strengths include the elaborate sham procedures and the SMS registration of outcomes, reducing recall bias. Finally, it should be noted that both the chiropractic manipulation group and the sham manipulation group are attended to by the same chiropractor at every visit, reducing the risk of equipoise bias in the treatment group, and ensuring that the exact same procedure is performed on all participants (except for manipulation/sham manipulation).

If it is possible to develop effective treatment for headache in children, a life course of recurring problems may be altered with potential positive implications for both individuals and society. And because there are no reports of serious side effects to this type of manipulative therapy in children in the scientific literature, besides temporary reddening and soreness, the possible implications in terms of improved health and wellbeing could be considerable.

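### The safety outcome omits occurrence and inherits an analysis of means that does not fit the type or duration of side effects

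*Protocol article*

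**What the plan says.** In the protocol article, the abstract names the safety outcome broadly: "Secondary outcomes include side-effects and headache status after one year". The operative list under Secondary outcomes is narrower. It covers what kind of side effect followed treatment and how long it lasted; whether one occurred is not listed.

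The analysis is set in one sentence of Statistical analyses: "Secondary outcomes will be analyzed similarly". The text it points back to contains:

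- Effect measure: "Intervention effects will be assessed by considering the difference in mean values between the two treatment arms", with 95% confidence intervals and p-values, plus Cohen's effect size.
- Model: "For all four primary outcomes, inference will be based on a least squares regression model".
- Covariate: "For each change score the baseline level will enter as covariate". Global perceived effect, which has no baseline of its own, is adjusted for headache days per week.
- Proportions: a responder analysis of the three change scores at four levels of improvement, and a number needed to treat with success defined as 20% improvement.

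On data collection, the Blinding section says that at all sessions, in both groups, the chiropractor asks about "side effects experienced after the previous treatment according to a checklist". The list of additional information collected by the chiropractor gives type, timing and duration of side effects at each visit, and the number of treatments.

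**The concern.** The basic safety question in a two-arm trial is how many children are affected in each arm. Here the outcome definition leaves that out, and the analysis assigned to what remains does not suit it:

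- Type is nominal. It has no mean, no Cohen's effect size and no least squares model.
- Duration exists only for a child who had a side effect. The document does not say whether unaffected children are left out or counted as 0. Leaving them out compares subsets formed after randomisation.
- Records are made per visit, while the model referred to takes one value per child.

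This is a stated rule that fits badly, not a detail left to a later document. The article itself says the literature reports no serious harms in children "besides temporary reddening and soreness", so some minor side effects are to be expected. Benefit would be given as a number needed to treat, with no figure for harm on a comparable scale.

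**Working it through.** **The plan's own figures.** There is none for side effects. The 100 per arm used below comes from Sample size considerations, where it is derived for headache days. It reproduces if the SD of 5.58 is read as days per four weeks: difference 4 × 0.55 = 2.2 days, n = 2 × (1.96 + 0.842)² × 5.58² / 2.2² ≈ 101 per arm. That figure says nothing about safety. Every rate and duration below is an assumption.

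**Illustration 1: equal durations.** Assume 30 of 100 affected under manipulation, 10 of 100 under sham, and every episode lasting 1 day.

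- Risk difference = 0.30 − 0.10 = 0.20. SE = √(0.3×0.7/100 + 0.1×0.9/100) = 0.0548. 95% CI = 0.20 ± 1.96 × 0.0548 = 0.093 to 0.307.
- Mean duration, affected children only: 30/30 = 1.0 day against 10/10 = 1.0 day, difference 0. Cohen's effect size is 0/0 here, so it is undefined rather than null.
- Mean days per child, unaffected counted as 0: 30/100 = 0.30 against 10/100 = 0.10. The direction is right.

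**Illustration 2: longer sham episodes.** As above, but 3 of the 10 sham episodes last 3 days.

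- Affected only: 1.0 day against (7×1 + 3×3)/10 = 1.6 days. Manipulation looks better.
- Unaffected counted as 0: 0.30 against 16/100 = 0.16 days per child. The direction is again right.

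**Range for the risk difference**, against 10% in sham and by the same formula: 20% gives 10 points (0.2 to 19.8); 40% gives 30 points (18.7 to 41.3).

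**Simulation.** 4,000 runs, 100 per arm, exponential durations, 40% affected under manipulation (mean 1 day) and 20% under sham. Entries are the share of runs with a result significant at 5%.

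| Sham mean duration | Affected only: shows harm | Affected only: favours manipulation | Unaffected as 0: shows harm | Proportions: show harm |
|---|---|---|---|---|
| 1 day | 2% | 3% | 54% | 88% |
| 1.5 days | 0.1% | 32% | 16% | 88% |
| 2 days | 0% | 72% | 4% | 88% |

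The affected-only comparison misses a difference in occurrence in every row; it reverses the direction only when sham episodes are longer. In the last row, days per child are equal by construction (0.40×1 = 0.20×2 = 0.40), so the 4% is not a failure of that test. It shows that total days can match while twice as many children are affected.

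**Power of comparing proportions** at 100 per arm, two-sided 5%: 30% v 10%, 95%; 40% v 20%, 88%; 30% v 15%, 72%; 20% v 10%, 51%; 5% v 1%, 38%. An estimate with its interval is therefore more useful than a test alone.

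**Exposure.** Sham has eight fixed visits; the active arm has a variable number. At an assumed 5% risk per visit, the chance of at least one side effect is 1 − 0.95⁴ = 19% over 4 visits, 1 − 0.95⁸ = 34% over 8 and 1 − 0.95¹² = 46% over 12. The share affected therefore has to be read beside the number of sessions.

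**The case against.** The strongest reply is that nothing forbids comparing occurrence. The abstract names side effects without restriction, per-visit checklist data exist in both arms, and the instruction to analyse similarly follows a paragraph that includes proportions. The plan also describes outcome distributions by arm, which for a categorical outcome would be a frequency table. This stands against the stronger reading that the share of children affected will never be compared: the document plans no such comparison but does not exclude one, and an analysis plan not shown may contain it. It does not remove the core. The planned proportions and number needed to treat are defined by headache improvement and do not carry over to side effects without a new definition.

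A reader might also infer that the planned analysis will hide or reverse a harm. The documents do not support that. Comparing duration among affected children only is one reading of a silent text. With unaffected children counted as 0, both illustrations keep the right direction, and reversal under the other reading needs longer sham episodes, for which the document gives no reason.

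Two smaller replies also stand. A missing baseline value is not a strong objection, because the plan already substitutes headache days for global perceived effect. And the stated aim is effectiveness; the need for safe treatment options appears as background, so safety should not be presented as a trial objective. Finer choices, such as a number needed to harm or whether to test duration, are matters for an analysis plan.

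**Conclusion.** The point holds in a limited form. The listed safety outcome omits occurrence, and the rule for secondary outcomes assigns it an analysis that cannot be applied to type and does not measure how many children are affected. No between-arm comparison of that share is planned in this document. If duration were compared among affected children only, a difference in occurrence would be missed; under some assumed inputs the direction would reverse. If unaffected children were counted as 0, the share affected would still not be reported.

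The document gives no side-effect rates, so the size is illustrative only: an unreported risk difference of 10 to 30 points for assumed rates of 20% to 40% under manipulation against 10% under sham. The defect itself does not depend on those rates.

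**What to change.** - Add occurrence to the secondary outcome, so that it covers occurrence, type and duration, and exempt it from the blanket rule for secondary outcomes.
- State that, for all children with at least one session, the number and proportion with at least one side effect are reported by arm, overall and by type, with the risk difference and 95% CI.
- Describe duration among affected children, labelled as such.
- Report the number of sessions per arm alongside. If a rate per session is given, count only sessions followed by a visit at which side effects were asked about. The enquiry concerns the previous treatment, and none is described after a child's last session.

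The cost is a few sentences in the analysis section and one word in the outcome list. The variables are already recorded at each visit, and nothing in treatment or visit schedules changes. The small downside is that the harm figure reported may look less favourable than a comparison of durations.

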## Discussion

Chronic or recurrent headache in children can have a negative impact on their participation, academic performance, physical health etc. [2, 3, 5]. Considering the potential long-term consequences of this, as well as the likelihood of pediatric headaches to continue into adulthood [6–8], it is important to develop safe and effective evidence-based treatment options. To our knowledge, this is the first randomized controlled trial investigating the effect of chiropractic manipulation on children with recurrent headaches. The results of the trial will inform future research in this area as well as clinical practice relating to non-pharmacological treatment of recurrent headache in children aged 7 to 14.

An adaptive design was chosen in relation to prioritizing the primary outcomes, as we cannot build on experience with these outcomes in this setting. Adaptive designs can be applied across all phases of clinical research and are more flexible by using results accumulated during the trial to modify the trial’s design or course in accordance with pre-specified rules [35]. Interim non-comparative analyses can be used to inform sample-size considerations as well as choice of outcome measure [36], which is particularly useful in areas where there are no established traditions or recommended core sets of outcomes, as is the case in this study. This design allows for correction of potential misjudgments in the priorities of outcomes [37], and since the interim analyses are pre-planned and performed by an independent statistician, the scientific standard is not compromised.

The involvement of only one practitioner performing all treatments ensures a high level of homogeneity in the treatments. However, it can also represent a weakness because the results of the treatment depend on the ability of only one practitioner. This weakness is accentuated by the poor reliability reported for palpatory findings [38] which are used to identify the biomechanical dysfunctions suitable for manipulative treatment.

The parent-child interaction may bias the answers of both child and parent [21] because there can be a discrepancy between the child and the parent’s report of the child’s headache [39]. Therefore, it is important that the same person reports on the text message headache diary every week during the entire trial and this represents a challenge for some children living in divorce families with inadequate communication between the parents. This is especially true for the SMS-question regarding use of medication because the children may not always be aware of what type of medication they receive and for what. Reporting of medication used can also depend on the age of the child. Some children are allowed to carry their own non-prescription medication for headache and use it according to own needs without asking the parents first, and therefore memory bias can be an issue in this age group.

A major strength of this study is its pragmatic nature, performed in a normal clinical setting, where the chiropractic manipulation treatment group receives treatment according to their individual needs in terms of areas in the spine being treated and the number of treatments given. In addition, parents and children in both groups can continue their usual self-care for headache if and when they want to. First of all, this allows us to investigate the specific effect of chiropractic manipulation and secondly, is a requirement for ethical reasons because we investigate children who suffer from recurrent and in some cases severe headache and/or migraine. Further strengths include the elaborate sham procedures and the SMS registration of outcomes, reducing recall bias. Finally, it should be noted that both the chiropractic manipulation group and the sham manipulation group are attended to by the same chiropractor at every visit, reducing the risk of equipoise bias in the treatment group, and ensuring that the exact same procedure is performed on all participants (except for manipulation/sham manipulation).

If it is possible to develop effective treatment for headache in children, a life course of recurring problems may be altered with potential positive implications for both individuals and society. And because there are no reports of serious side effects to this type of manipulative therapy in children in the scientific literature, besides temporary reddening and soreness, the possible implications in terms of improved health and wellbeing could be considerable.

